There are 71 ongoing or completed clinical trials (as of 30 November, 2004) in which Montanide®ISA51 is used as an adjuvant (reference [http://clinicaltrials.gov/](http://clinicaltrials.gov/ct/gui) ). These include data from trials which have been published, others that are no longer recruiting or are completed (37 trials), and ongoing studies (34 trials), which are projected to recruit a cumulative 10,060 subjects when completed. Local reactions at the injection site are the most common findings, estimated by one principal investigator to be present in virtually all recipients, with approximately 15% of Montanide®ISA51 recipients having moderate (Grade 2) local reactions. The reactions were described as induration and occasional superficial ulcerations at the injection site. The vaccine was delivered subcutaneously in these trials. These reactions occurred in both initial and subsequent injections (in different individuals), and resolved within days without surgery or antibiotic treatment.

Abscess formation has been observed in one unpublished study, in which Montanide®ISA51 was used as an adjuvant with an HIV-derived, HLA binding peptide, at a dose range of 1-4 mg of the immunogen in 2 mL of Montanide®ISA51 formulation and delivered and in 4 x 0.5 mL injections) to healthy volunteers ([name], personal communication). In this trial, cold abscesses occurred in four of twenty recipients of Montanide®ISA51 two to four weeks after vaccination. These reactions were classified as Grade 3 local reactions. Volunteers with the abscesses had received either 1 mg or 4 mg of the immunogen. Two abscesses occurred after the first injection and two occurred after the second injection. All four required surgical drainage, but showed no evidence of infection.

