## Enrollment

Volunteers will respond to advertisements distributed by the clinical trial site in local newspapers and posted flyers (See **Appendix A**). A screening visit will be scheduled after an initial contact screen by clinical trial staff, consisting of background information of the trial (**Appendix B**). During this initial screening visit, the volunteer will read the consent form and be encouraged to ask questions, and then take a multiple-choice questionnaire to evaluate consent comprehension (**Appendix C**). The volunteer must answer all questions correctly prior to being eligible for enrollment. Study staff will use incorrect answers from the questionnaire to identify those areas of the informed consent form that need further review with the volunteer. This will help ensure the volunteer has sufficient understanding before the consent form is signed. The volunteer may either sign the consent form during the screening visit or return after further consideration. Seventy two volunteers will be enrolled and assigned to one of 6 vaccine groups (5 µg, 20 µg or 80 µg of PpPfs25/ISA51 or ScPvs25/ISA51). There will be 10 volunteers in each group randomized to receive vaccine and 2 volunteers in each group randomized to receive placebo. Therefore, each of the 6 groups will have 12 volunteers each.

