### Description of the Statistical Methods to Be Employed

The purpose of this trial is to estimate event rates and patterns of immune responses as well as to compare these rates and patterns in different doses of the study vaccines and to compare the response by the two vaccines. This section briefly describes the statistical methods to be used. A detailed analytic plan will fully describe the methods. The analytic plan will discuss the planned approaches to missing data. Listings will show all observed data and, if applicable, impute values and the approaches taken for imputation.

Estimates will be presented with their 95% confidence intervals. Descriptive approaches will be used to meet the protocol objectives as stated in **Section** **2.0** of this protocol. In particular, the immunologic response for each of the 72 volunteers will be presented as individual graphs,

and all adverse events will be listed. Formal statistical tests, as outlined below, will be used to compare doses.

Statistical tests on the adverse event data will be performed without correction for multiplicity, because typically the family-wise Type I error is not bound for tests of safety. A nominal Type I error rate of 10 percent will be used. Most of the analyses of immunogenicity will be based on a longitudinal mixed model with terms for dose group for each of the 2 vaccines.

Primary Objective: To assess the safety, reactogenicity, and immunogenicity of the PpPfs25/ISA51 and ScPvs25/ISA51 malaria vaccines.

1. Summarize the frequency of immediate, systemic and local AEs.
2. Line listing of individual clinical and laboratory AEs as classified by immediate (within the first 30 minutes), systemic and local will be displayed in tabular format and stratified by dose cohort.
3. AEs will be summarized by severity and relationship to vaccine by individuals and dose cohort.

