4. The proportion of volunteers with at least one local adverse event will be compared by dose cohort for each vaccine.  Formal statistical tests will assess whether the three cohorts differ with respect to these proportions, and whether there is a dose-response relationship. To see if there is a difference in adverse events between the initial vaccination and the subsequent vaccination we perform a sign test, where the response for each volunteer is the difference between the number of adverse events in the 60 days following the first vaccination and the number of adverse events in the 60 days following the second vaccination.
5. To determine the dose that generates the highest serum antibody levels to homologous antigen at Day 150 (1 month after the second immunization).

 i.   A Kruskal-Wallis test will be performed to check for any significant differences in the antibody concentrations of the three dose groups.  If that test is significant, then all three pairwise Mann-Whitney tests will be performed to see which pairs have significant differences. If the Kruskal-Wallis test is not significant then we will not perform any Mann-Whitney tests on the pairs of dose groups.  All of the tests can be performed at the 0.05 level and they will retain a family-wise error rate of 0.05

Secondary Objective 1: To assess and compare the duration of specific antibody response to homologous Pfs25 or Pvs25 over an 18 month period.

1. Describe immunogenicity responses by vaccine and dose group, over time.
2. Individual responses will be described over time and stratified by dose cohort.
3. Antibody concentration will be measured at Days 0, 14, 30, 60, 90, 120, 134, 150, 180, 270, 360 and 556. To exploit the multiple measures of antibody within each subject, a longitudinal model will be built to describe the antibody response over time. The model will explore if there are any differences between Pfs25 and Pvs25 and explore dose effects.

Secondary Objective 2: Measure the effect of boosting at 4 months on antibody units.

1. Using difference in antibody level from Day 0 to Day 150 as the response, exact Jonckheere-Terpstra tests will be performed to determine if there is a dose response. Using the same response, exact stratified Wilcoxon rank sum tests, stratified on dose level, will be performed to determine if there are differences between the dose groups. If feasible, similar tests may be done using the longitudinal model described above.

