### Safety

The primary safety endpoint is the frequency and severity of vaccine-related AEs, as classified by both intensity and severity through active and passive surveillance. Separate assessments of systemic and local reactions will be performed.

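### The only adverse-event response formally compared between doses is any-grade local reaction, which ignores severity and may sit near its ceiling

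*Protocol*

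**What the plan says.** Section 9.1.1, Primary Objective item 4, names the response: "The proportion of volunteers with at least one local adverse event will be compared by dose cohort for each vaccine". Two tests are then applied to it: "Formal statistical tests will assess whether the three cohorts differ with respect to these proportions, and whether there is a dose-response relationship". The level is set a little earlier in the same section: "A nominal Type I error rate of 10 percent will be used", without correction for multiplicity.

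No grade threshold is attached to the response. In Table 3 (section 7.2.2), easily tolerated pain, or any erythema, swelling or induration above 0 mm, is already Grade 1. One such finding after either injection therefore makes a volunteer an event.

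The other formal adverse-event test in item 4 does not compare doses: "To see if there is a difference in adverse events between the initial vaccination and the subsequent vaccination we perform a sign test". Severity by dose cohort appears only as a summary (item 3).

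Section 9.1.2 reads: "The primary safety endpoint is the frequency and severity of vaccine-related AEs".

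On how often local reactions occur with this adjuvant, section 1.4.3 gives two figures. One is a pooled 55% of 1862 subjects in 27 trials. The other describes local reactions as "estimated by one principal investigator to be present in virtually all recipients, with approximately 15% of Montanide®ISA51 recipients having moderate (Grade 2) local reactions", from trials that used the subcutaneous route. Neither is adopted as a planning rate.

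**The concern.** Two separate problems arise.

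The first holds at any background rate. The response is a yes/no on any local reaction, so a volunteer who moves from Grade 1 to Grade 2 or 3 at a higher dose counts the same before and after. The severity half of the primary safety endpoint has no formal comparison between doses. Yet graded local reactions are what the protocol watches most closely: one criterion in section 7.5 turns on Grade 2 or higher induration, and section 10.3.2 reports that severe swelling or induration has already been seen with these vaccines.

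The second is conditional. All vaccines carry the same amount of Montanide (section 3.1) and the placebo contains it too (section 5.1). Each volunteer gets two injections, keeps a diary for 20 days after each (section 6.6) and has the site examined repeatedly. If almost everyone then reports some local reaction, all three proportions lie near 100% and the test has almost nothing to detect.

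Section 9.1 says the results will guide dosing in later trials, so an uninformative dose comparison of reactogenicity has a cost.

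**Working it through.** **The plan's own figure.** The only adverse-event operating figure is in section 9.2: 0.80 probability of at least one serious or severe event with 10 volunteers at a rate of 0.15. It reproduces: 1 − 0.85^10 = 0.803. No power is stated for the local-reaction comparison.

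**Inputs.**
- Sample size (section 6.2): "There will be 10 volunteers in each group randomized to receive vaccine and 2 volunteers in each group randomized to receive placebo". I use 10 vaccinees at each of three doses and leave placebos out.
- Level: 0.10 (section 9.1.1). Sidedness is not stated; two-sided is assumed.
- Test: item 4 names none. I use the exact conditional trend test with equally spaced scores, enumerating all 11^3 outcomes, with the Freeman-Halton test for heterogeneity.
- Event rates: assumed, anchored on section 1.4.3.

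**What rejection requires near the ceiling.** Suppose the upper two cohorts are both 10/10.
- Low dose 8/10: the chance that both non-events fall in that cohort is C(10,2)/C(30,2) = 45/435 = 0.103. Trend p = 2 × 0.103 = 0.21; Freeman-Halton p = 3 × 0.103 = 0.31.
- Low dose 7/10: C(10,3)/C(30,3) = 120/4060 = 0.0296. Trend p = 0.059; Freeman-Halton p = 0.089.

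So the low-dose cohort must fall to 7/10 or below.

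**Power by hand for 95/98/100%.** The top cohort is always 10/10. Rejection needs essentially one of:
- low 7 and middle 10: 120 × 0.95^7 × 0.05^3 × 0.98^10 = 0.01048 × 0.817 = 0.0086
- low 6 and middle at least 8: about 210 × 0.95^6 × 0.05^4 = 0.0010
- low 5: about 0.0001

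The total is about 0.010.

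**Full enumeration (any-grade rates, assumed).**

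| Rates at 5/20/80 µg | Exact trend | Freeman-Halton |
|---|---|---|
| 95/98/100% | 0.010 | 0.010 |
| 90/95/99% | 0.043 | 0.047 |
| 85/95/100% | 0.13 | 0.13 |
| 80/90/100% | 0.19 | 0.18 |
| 55/70/85% | 0.33 | 0.28 |
| 55/75/95% | 0.59 | 0.49 |

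With a common rate of 95%, the trend test rejects in 0.9% of trials against a nominal 10%.

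**Blindness to severity (hypothetical counts).** Let all 30 vaccinees have some local reaction, with Grade 2 or higher in 1/10, 4/10 and 7/10. The any-grade table is 10/10, 10/10, 10/10, so p = 1. On Grade 2 or higher there are 12 events. The tables in which the high-minus-low difference is at least 6 have total weight 492,505 out of C(30,12) = 86,493,225, so the two-sided trend p = 2 × 492,505 / 86,493,225 = 0.011.

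**What a graded response can gain.** At equal gradients a Grade 2 or higher threshold is no more powerful than the any-grade response away from the ceiling: 15/30/45% gives 0.33, the mirror image of 55/70/85%. Shallow gradients are mostly missed: 15/25/35% gives 0.19 and 15/20/25% gives 0.08. A rank trend test on the worst grade uses both kinds of shift. In simulation with any-grade 55/70/85% and assumed Grade 2 or higher gradients, its power was about 0.41 to 0.55 against 0.33, with a rejection rate of about 0.09 under no dose effect. These figures depend on the assumed grade distributions.

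**The case against.** A reader might infer that the protocol itself expects local reactions in nearly every recipient, so that the test is certain to sit at its ceiling. The documents do not say this. The high figure is one investigator's estimate from subcutaneous trials, whereas this trial injects intramuscularly (section 6.4), and the pooled figure is 55% of subjects. If 55% applied per injection and independently to two injections, the per-volunteer rate would be 1 − 0.45^2 = 0.80. But section 1.4.3 states it per subject, so that is only an assumption. The ceiling is a plausible risk and no more.

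A reader might also infer that a dose-related rise in severe local reactions would go unreported. That is not supported either. Adverse events are listed and summarized by severity and dose cohort, estimates carry 95% intervals, and the Safety Monitoring Committee reviews all local events before each escalation (section 7.5). If, for example, 40% of a cohort had Grade 2 or higher induration, the chance that at least 3 of 10 did would be 1 − (0.6^10 + 10 × 0.4 × 0.6^9 + 45 × 0.4^2 × 0.6^8) = 0.83, which would reach the number in the section 7.5 criterion. What is missing is a formal comparison.

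A third tempting step is to set power of 65% for Grade 2 or higher at 15/40/65% against 33% for any grade at 55/70/85%. That compares a 50-point with a 30-point rise. No steep gradient is supported by the document: section 1.4.1 attributes the injection-site inflammation in rabbits mainly to the adjuvant.

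Finally, section 9.1.1 defers detail to an analytic plan that is not shown, and that plan could add a graded test. This stands in part. The protocol nevertheless fixes the tested response itself, and fixes it without severity.

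**Conclusion.** The point holds in a limited form. The one adverse-event response formally compared between doses is an any-grade proportion. It leaves out the severity half of the primary safety endpoint and cannot register a shift from Grade 1 to a higher grade. That follows from the definition and needs no assumption about rates.

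The ceiling is conditional. If the virtually-all estimate carries over to this trial, exact trend power is about 1% to 4% for the rates assumed above. Under the pooled 55% it is about 33% for a 30-point rise, which is low because there are 10 per dose, not because of a ceiling.

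The results assume 10 vaccinees per dose, a two-sided 10% level and exact tests. A graded response does not make the trial well powered, since only large gradients are detectable. The change is worth making because it brings the test into line with the endpoint at almost no cost.

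**What to change.** In section 9.1.1, item 4, make the formally tested response each volunteer's worst local-reaction grade (0 to 3, Table 3) over both vaccinations. Compare it across the three doses of each vaccine with an exact ordered trend test, such as the exact Jonckheere-Terpstra test already planned for the antibody response, and state whether it is one- or two-sided. Report the proportion with Grade 2 or higher per dose with an exact 95% confidence interval, and keep the any-grade proportion as description. Adding the pooled placebo recipients as dose zero is optional.

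The cost is a small change of analysis wording. Table 3 grades are already collected, so no visit, assessment or sample size changes. The downside is that the tested result becomes a shift in grade and is less simple to state than a difference in proportions.

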## Tertiary Objectives

1. To measure the ability of vaccine induced antibody to inhibit oocyst development in a mosquito membrane feeding assay
2. To determine the relationship between antibody levels and degree of transmission blocking in a membrane feeding assay
3. This study will form the basis of further transmission blocking vaccine development, including the establishment of human standards for immune assays.

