## Immunologic Testing

### Antibody Assay (ELISA)

Serum antibody levels to the Pfs25 and Pvs25 antigens will be measured by ELISA. Briefly, microwell plates (Dynex Technologies) are coated overnight at 4oC with 100 μL/well of antigen solution (1 μg/mL). Plates are washed with TRIS-buffered saline (TBS) containing 0.1% Tween‑20 (0.1% T-TBS) and blocked with TBS containing 5% skim milk powder for 2 hours at room temperature. After washing with 0.1% T-TBS, serum samples at a dilution of 1:5,000 in 0.5% T-TBS containing 5% skim milk powder are added in triplicate and incubated for 2 hours at room temperature. After incubation, unbound antibodies are removed by washing the plates with 0.1% T-TBS, and 100 μL of alkaline phosphatase-conjugated goat anti-human IgG solution (Kirkegaard & Perry Labs, Gaithersburg, Maryland, 1:1,000 dilution in 0.5% T-TBS containing 5% skim milk powder,) is added to each well and incubated for 2 hours at room temperature. Plates are then washed with 0.1% T-TBS, followed by adding 100 μL of phosphatase solution (Sigma, St. Louis, Missouri) to each well; the plates are then covered with aluminum foil and incubated for 20 minutes at room temperature for color development. The plates are read immediately at 405 nm with a microplate reader (Spectramax 340PC Molecular Devices). The optical density values are used to determine anti-Pfs25 and anti-Pvs25 antibody concentration by comparison to a standard curve generated with known positive control sera included on each ELISA plate.

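### Between-vaccine comparisons of antibody level or raw change in Section 9.1.1 are not interpretable unless the Pfs25 and Pvs25 ELISAs share a calibration, which the protocol does not describe

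*Protocol*

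**What the plan says.** Section 9.1.1 of the protocol gives as a purpose of the trial "to compare these rates and patterns in different doses of the study vaccines and to compare the response by the two vaccines". Three parts of that section bear on the between-vaccine comparison.

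- Under Secondary Objective 1, which is about duration, one longitudinal model covers both vaccines: "The model will explore if there are any differences between Pfs25 and Pvs25 and explore dose effects".
- Under Secondary Objective 2, the response is the difference in antibody level from Day 0 to Day 150, and "exact stratified Wilcoxon rank sum tests, stratified on dose level, will be performed to determine if there are differences between the dose groups".
- Also under Secondary Objective 2, the rise from Day 120 to Day 150 is to be estimated and compared. The text does not say between whom, or whether as a difference or a ratio.

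The measurement is described in Section 6.8.1. Optical density is converted to an antibody concentration "by comparison to a standard curve generated with known positive control sera included on each ELISA plate". The analysis concerns the homologous antigen, so the PpPfs25 groups are read for anti-Pfs25 and the ScPvs25 groups for anti-Pvs25. No unit, shared reference or conversion between the two assays is stated. The restated Secondary Objective 2 reads "Measure the effect of boosting at 4 months on antibody units", whereas other places say concentration or level.

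**The concern.** Antibody to Pfs25 and antibody to Pvs25 are different analytes. If each assay's scale depends on how values were assigned to its control sera, one unit of anti-Pfs25 need not represent the same amount of antibody as one unit of anti-Pvs25. A vaccine main effect in the joint model, or a rank test of one vaccine against the other on level or raw change, would then carry that unit ratio as well as any biological difference. The text sets no limit that would prevent this: a search for any differences includes a difference in level, and subtracting Day 0 from Day 150 does not remove the unit.

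At stake is the reading of a secondary, partly exploratory comparison. The report could describe one antigen as inducing more antibody when the data cannot show it.

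**Working it through.** **What the stratified Wilcoxon test can compare.** Within a stratum of one dose level there is no dose contrast. Among vaccinated volunteers the only contrast left is PpPfs25 against ScPvs25, 10 against 10 in each of three strata. (Placebo volunteers also sit in each cohort, but the sentence does not mention them.) The stated aim of comparing dose groups therefore does not fit the stated stratification.

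**How the unit enters.** Let the recorded value be U = c × A, where A is true antibody and c is specific to the assay. Put k = c_Pfs / c_Pvs.

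- Level: ln U_Pfs − ln U_Pvs = (ln A_Pfs − ln A_Pvs) + ln k. The contrast shifts by ln k.
- Raw change: U(150) − U(0) = c × [A(150) − A(0)]. The factor c remains.
- Ratio over time: ln[U(150)/U(120)] = ln[A(150)/A(120)]. The factor c cancels.
- Slope of ln U on ln dose within a vaccine: c goes into the intercept only and leaves the slope unchanged.

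**Spread.** Section 9.2 gives a coefficient of variation of 1.2 to 1.4. Read as lognormal, SD(ln) = √ln(1 + CV²): √ln(2.44) = 0.944 and √ln(2.96) = 1.042.

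The concern has no stated figure of its own to reproduce. As a check on these inputs, the five-fold difference in Section 9.2 with 10 per group gives a simulated Mann-Whitney power of 0.93 (CV 1.2) to 0.87 (CV 1.4) at two-sided 0.05. This is above the stated 0.80 and so supports the claim of detecting at least five-fold.

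**Size of the distortion.** k is not in the documents, so it is assumed over 0.1 to 10. Both vaccines were given identical true responses and one assay's unit was multiplied by k. The dose-stratified Wilcoxon test (three strata of 10 against 10, normal approximation, two-sided 0.05, 4,000 runs) was applied to log level and to a within-volunteer log ratio of a later day to Day 150. The last column is an exact Mann-Whitney test at one dose (3,000 runs). Ranges run over CV 1.2 to 1.4.

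| Assumed k | Rejects on level | Rejects on log ratio | Rejects on level, one dose |
|---|---|---|---|
| 0.2 | about 100% | 5.0–6.2% | 87–92% |
| 0.5 | 69–76% | 4.8–5.0% | 25–30% |
| 1 | 5.4–5.6% | 5.4–5.7% | 4.3% |
| 2 | 67–77% | 5.0–5.6% | 26–31% |
| 5 | about 100% | 5.0–5.8% | 86–93% |

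At k = 0.1 and 10 the stratified level test rejects always, and the log-ratio test stays at 4.8 to 5.3%. With a wider SD(ln) of 1.3, the stratified level test rejects in about 50% at k = 0.5 or 2 and about 99% at k = 0.2 or 5.

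The level test stands in for the planned test on raw change. The two rank volunteers almost alike when Day 0 values are small beside Day 150, which is an assumption here.

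**The case against.** The strongest reply is that the protocol never says the units are arbitrary or that each assay has its own reference sera. Section 6.8.1 speaks of concentration, the word units appears only in the restated objective, and how the control sera got their values belongs to the assay procedure. That stands. A reader might infer that a between-vaccine difference in level has no meaning at all. The documents do not support that, because if both curves were calibrated in mass units a level comparison would have some meaning. Nor does the tertiary objective that mentions "including the establishment of human standards for immune assays" settle it: it concerns future development and does not say that the present ELISA is uncalibrated.

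A second reply is that the model sentence is exploratory, sits under "To assess and compare the duration of specific antibody response to homologous Pfs25 or Pvs25 over an 18 month period", and can be read as vaccine-by-time contrasts, which are sound on the log scale. Section 9.1.1 ties formal tests to doses and defers detail to an analytic plan. This limits the point but does not remove it. The protocol itself states the purpose "to compare the response by the two vaccines", itself chooses a raw difference as the response, and itself stratifies on dose a test said to compare doses. A later plan can add detail, but it cannot make uncalibrated levels comparable.

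A third reply concerns harm. A reader might infer that a false ranking would misdirect the combination vaccine. Section 1.5 makes that step depend on each component showing safety and immunogenicity, not on which gives more antibody, so this harm is not supported.

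Finally, c cancels from ratios only if the standard curves are parallel and values lie within assay range. Section 6.8.1 reads sera at a single dilution of 1:5,000, so low Day 120 values could fall near the floor. This caveat carries over to the fix.

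**Conclusion.** The point holds in a limited form. The protocol plans between-vaccine comparisons that include level and raw change, describes no common calibration for two assays on different antigens, and words the dose-stratified Wilcoxon test so that its stated purpose and its construction disagree. Unless a shared calibration exists, a between-vaccine difference in level or raw change cannot be read as one vaccine inducing more antibody.

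The size depends on k, which is unknown. At k = 1 there is no distortion. At an assumed two-fold ratio, equal responses would be declared different in about 67 to 77% of trials, given lognormal responses with the CV in Section 9.2. The log-ratio test stays near 5% throughout.

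The Day 150 dose comparison under the primary objective is unaffected when run within each vaccine, as are other within-vaccine contrasts. No stated decision depends on ranking the antigens. This should be corrected, but it does not threaten the main conclusions of the trial.

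**What to change.** In Section 9.1.1:

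1. Limit between-vaccine inference to log-scale quantities in which the unit cancels: Day 150/Day 120; Days 180, 270, 360 and 556 each over Day 150; and the slope on log dose.
2. In the longitudinal model, fit vaccine-specific intercepts, interpret the vaccine-by-time and vaccine-by-dose terms, and do not interpret the vaccine main effect.
3. Reword the stratified Wilcoxon test to say what it compares. If it compares the vaccines, run it on a log ratio such as Day 150/Day 120 instead of the raw Day 0 to Day 150 difference.
4. Compare levels between vaccines only if both assays are calibrated to a common mass unit, and if so state that calibration in Section 6.8.1.
5. State that the ratios rely on parallel standard curves and values within assay range.

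This changes wording only and needs no new samples or visits. The cost is that the question of which antigen gives more antibody is dropped unless a common calibration exists.
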